# Enrollment procedure and randomization

- 1. **Enrollment procedure**

Confirm using the registration eligibility confirmation sheet that the target patient meets all the eligibility criteria and does not meet the exclusion criteria, and register at the time of hospitalization for surgical purposes. Register on a password-managed computer of the office in the department of Anesthesia and Intensive Care on the 8th floor of the National Cancer Center Hospital.

Contact:: Research office([name]) TEL：[name] FAX：[name]

- - 1. **Notes on registration**

1. Registration after the start of protocol treatment is not tolerated without exception.
2. Registration is done on a password-managed computer in the Department of Anesthesia and Intensive Care Medicine on the 8th floor of the National Cancer Center Hospital.
3. Eligibility is confirmed using the registration eligibility confirmation sheet, and the confirmation sheet is stored in the Department of Anesthesia and Intensive Care Medicine on the 8th floor of the National Cancer Center Hospital.
4. Registration is completed when two researchers confirm that the contents of the registration eligibility confirmation form and the data at the time of registration are entered on the computer.
5. Except in the case of withdrawal of consent including refusal to use the data for the study, patients once enrolled will not be deregistered.
   1. **Randomization**

Patients will be randomly assigned to enroll by researchers who are not involved in consent and anesthesia. No adjustment factor is provided, and random allocation is performed using the substitution block method.

- 1. **Procedures for Termination of Registration**

When the planned number of registrations is expected to be achieved in this study, the Research Office will inform the researcher..Researchers will not explain to new patients after the planned number of registrations is reached.the Research Office closes registration at 5 p.m. on the Friday following the date on which the expected number of registrations is registered.

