## Criteria for Discontinuation of Protocol Treatment

## Discontinue protocol treatment if adverse events are observed in which each group-assigned drug is suspected.

# Expected adverse events

- 1. **Expected adverse events**
     1. **Adverse events expected with the drug**

According to the drug package insert

- - 1. **Adverse reactions and surgical complications expected by surgery**

1. Anesthesia-related complications

Fever^*1^, allergic reaction, inability to secure airway, acidosis^*1^, hyperkalemia^*1^, delirium, hoarseness, hematoma^*2^, catheter-related infection^*3^

*1 Items assuming malignant high fever expected as a complication of general anesthesia

*2 Items assuming epidural hematoma and spinal cord subarachnoid hematoma expected as complications of epidural anesthesia

*3 Items assuming epidural abscess and spinal cord subarachnoid abscess expected as complications of epidural anesthesia

1. Surgical complications

Damage to other organs, biliary fistula (about 10%), postoperative hemorrhage, infection (about 10%), liver failure (less than 0.1%), pulmonary embolism, death (less than 0/1%)

- 1. **Evaluation of adverse events/reactions**

To assess adverse events/reactions, the "JCOG postoperative complications criterion (Clavien-Dindo classification)" is used.

- - 1. **Grading of adverse events**

When grading adverse events, grading is the closest to the definition of grades 0 to 4, respectively. Also, when a specific treatment is described in grade, grading is performed from the clinical necessity. For example, the patient's pleural effusion may be increasing and the patient may refuse oxygen inhalation or chest drainage despite the indication of the situation. In such cases, grading is based on a medical judgment of what should be done, not what was actually done.

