# Evaluation items, clinical tests, and evaluation schedule

- 1. **Items to be collected before registration (using information from the anesthesiology preoperative outpatient clinic)**

Patient background (age, sex, primary cancer type, preoperative complications [Charlson Index], presence or absence of preoperative chemotherapy [drug used if performed], allergic history), ASA-PS, biochemical tests (AST, ALT, Bil)

- 1. **Observation period**

The observation period will be up to 28 days after surgery to assess postoperative complications in both groups. If protocol treatment is discontinued in any group, no observation period is set.

- 1. **Items to be collected during the treatment period**

Surgical method, anesthesia method, operative time, anesthesia time, number and total weight of resected liver, total ischemic time, intraoperative blood loss, intraoperative fluid/transfusion volume, intraoperative urine volume.

- 1. **Evaluation items after the end of treatment**
     1. **Primary outcome**
- Liver damage:

Assessed with the highest value of AST 3 days postoperatively.

In addition, the results of postoperative biochemical tests (tested daily for 3 days after surgery) that are usually performed in clinical practice will be used, and blood collection and testing for this study will not be performed.

- - 1. **Secondary outcome**
- Liver damage

As a particularly important secondary endpoint, the highest ALT value at 3 days postoperatively will be evaluated. In addition, the results of postoperative biochemical tests (tested daily for 3 days after surgery) that are usually performed in clinical practice will be used, and blood collection and testing for this study will not be performed.

- Early postoperative liver function evaluation

Assessed at the highest value of Bilirubin 3 days postoperatively. In addition, the results of postoperative biochemical tests (tested daily for 3 days after surgery) that are usually performed in clinical practice will be used, and blood collection and testing for this study will not be performed.

- Postoperative adverse event

JCOG postoperative complication criteria (Clavien-Dindo classification) Collect postoperative complications of grade II or higher for 28 days postoperatively.

- 1. **Evaluation Schedule**

|  | pretreatment | postoperative | | | |
| --- | --- | --- | --- | --- | --- |
|  | Anesthesiology outpatient | Day 1 | Day 2 | Day 3 | 〜 28 days |
| Characteristics | ○ | - | - | - | - |

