| ASA-PS | ○ | - | - | - | - |
| AST | ○ | ○ | ○ | ○ | - |
| ALT | ○ | ○ | ○ | ○ | - |
| Bilirubin | ○ | ○ | ○ | ○ | - |
| Postoperative advese event | - | ○ | ○ | ○ | ○ |

1. **Effect Determination and Endpoint Definition**

Including animal experiments, transaminase values are used as an evaluation item for ischemia-reperfusion injury in the liver region.^13)^ In clinical studies on ischemic reperfusion disorder after liver resection, the highest transaminase values in the early postoperative period have been used. ^5)-11)^ Since the purpose of this study is to evaluate ischemic reperfusion damage in the liver region, it will be adopted as a primary endpoint. Based on previous studies including retrospective studies (especially those by Beck-Schimner et al.), AST was considered to be more useful than ALT, and AST was selected as the primary endpoint in this study, and ALT was analyzed as an important secondary endpoint. There is no difference in the effect on postoperative AST and ALT between 15 and 30 minutes for one blood flow blockade.^16)^。

IRI is a condition that can adversely affect the whole body, and serious postoperative complications are considered to be important endpoints. However, since this study included metastatic liver tumor resection to assess the effect of anesthetics on IRI, the incidence of serious postoperative complications is expected to be very low (the incidence of serious complications after metastatic liver tumor resection in our hospital in the last two years is 1%). Therefore, it was set as a secondary endpoint. In addition, Bil, which is also an important endpoint, because severe ischemia-reperfusion injury disorder can cause liver damage from the early postoperative stage. However, as with serious postoperative complications, early postoperative liver damage is very unlikely, so it was set as a secondary endpoint.

- 1. **Define the target population**

Following the intent-to-treat principle, the analysis will be a population consisting of all randomized cases excluding cases with no data on the randomized primary endpoint (Maximum Analysis Set (FAS)).In addition, when discontinuation of protocol treatment occurs, analysis will be performed in a population of patients who have completed protocol treatment (Per Protocol Set: PPS).

- 1. **Defining Endpoints**
- Primary endpoint

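### Patients whose protocol treatment is stopped for suspected drug harm get no 28-day complication follow-up, against the stated intention-to-treat analysis

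*Protocol*

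**What the plan says.** Under Evaluation items, clinical tests, and evaluation schedule, the observation-period paragraph has two sentences: "The observation period will be up to 28 days after surgery to assess postoperative complications in both groups", and then "If protocol treatment is discontinued in any group, no observation period is set".

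Under Criteria for Discontinuation of Protocol Treatment there is a single criterion: "Discontinue protocol treatment if adverse events are observed in which each group-assigned drug is suspected".

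The section headed Define the target population sets the analysis population in these words: "Following the intent-to-treat principle, the analysis will be a population consisting of all randomized cases excluding cases with no data on the randomized primary endpoint". A per-protocol set is added for one situation: "when discontinuation of protocol treatment occurs, analysis will be performed in a population of patients who have completed protocol treatment".

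The notes on registration say that, apart from withdrawal of consent that includes refusal of data use, "patients once enrolled will not be deregistered".

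For AST, and in the same words for ALT and bilirubin, "the results of postoperative biochemical tests (tested daily for 3 days after surgery) that are usually performed in clinical practice will be used", with no sampling for the study itself. Complications of grade II or higher are a secondary endpoint, collected for 28 days and compared by Fisher's test.

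**The concern.** The patients who lose their observation period are selected by an event after randomisation, and that event is suspected harm from the randomised drug. Missing data of this kind are tied to treatment and possibly to outcome. If one drug is stopped more often than the other, complications after stopping go uncounted in that arm and the drug looks safer than it is.

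An intention-to-treat analysis needs outcome data from patients who stop treatment. The protocol claims the principle and in another section withdraws the data that it requires. The complication endpoint is directly affected. The primary endpoint may be affected too, depending on how the sentence is read.

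**Working it through.** **1. The passages side by side**

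| Place in the protocol | What it implies for a discontinued patient |
| --- | --- |
| Observation period | No observation period |
| Criteria for Discontinuation | The patient had an adverse event with the assigned drug suspected |
| Define the target population | In the FAS if AST data exist; outside the PPS |
| Notes on registration | Stays enrolled unless consent to data use is withdrawn |
| Planned number of registrations, registration period, tracking period | Followed for 28 days, no exception |
| Informed consent, duration of participation | Takes part from surgery to day 28, no exception |
| Evaluation Schedule | AST, ALT and bilirubin on days 1–3 and complications to day 28, no exception |

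One sentence stands against the rest, and no other section restores follow-up.

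**2. Which endpoints are affected**

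- *Complications.* The observation period is defined by its purpose of assessing complications. Removing it removes this endpoint. The Fisher test has no rule for such patients, who would be either dropped or counted as free of events.
- *AST, ALT, bilirubin.* These are listed separately and taken from routine daily tests, so values probably exist in the chart. The protocol does not say whether they may be used after discontinuation. If not, the patient leaves the FAS through the exclusion for missing primary endpoint data.

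**3. Size for complications**

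Inputs: 28 per group, 56 in total, and a 1% rate, all from the protocol.

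- Expected events: 56 × 0.01 = 0.56.
- Probability of at least one event: 1 − 0.99^56 = 0.43.

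Suppose, as an upper bound, that k patients in one arm are discontinued, each has a complication, and there are no other events:

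| k | Full follow-up | Fisher p | Shown under the rule |
| --- | --- | --- | --- |
| 1 | 1/28 (3.6%) vs 0/28 | 1.00 | 0/27 vs 0/28 |
| 3 | 3/28 (10.7%) vs 0/28 | 0.24 | 0/25 vs 0/28 |
| 6 | 6/28 (21.4%) vs 0/28 | 0.023 | 0/22 vs 0/28 |

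The last column drops unobserved patients. Counting them as free of events gives 0/28 in both arms.

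The 1% rate matters here. The list of surgical complications puts biliary fistula and infection at about 10% each, without a grade. If many of those were grade II or higher, one or two patients could no longer hold every event, though the selection would remain.

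**4. Size for AST, if AST is also lost**

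If k patients in an arm of 28 have peaks lying x above the mean of that arm's other patients, leaving them out lowers the arm mean by k × x / 28. Both k and x are assumptions.

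| k | x = 300 U/L | x = 600 U/L |
| --- | --- | --- |
| 1 | 10.7 | 21.4 |
| 2 | 21.4 | 42.9 |
| 3 | 32.1 | 64.3 |

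The range is about 11 to 64 U/L. The target difference is 300 U/L, and the standard error of the difference at the stated SD is 300 × √(2/28) = 80 U/L.

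**5. Power**

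The stated 28 per group serves here only as a denominator. It does not follow from its own inputs: 2 × (1.960 + 0.842)² × (300/300)² = 15.7, or 16 per group (17 by the exact t-test), while an SD of 400 gives 28. That is a separate matter. Losing three patients per arm takes power from 0.957 to 0.934 at SD 300, or from 0.787 to 0.738 at SD 400. Power is a minor issue; selection is the main one.

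**The case against.** A reader might infer more: that the primary endpoint is lost by rule, and that the FAS collapses into the PPS so that comparing them tells nothing. The documents do not support this, for four reasons.

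- The observation period is tied to complications. The biochemistry sits under a different heading with no exception for discontinuation. Loss of AST is one reading of an unclear sentence.
- Adding a PPS when discontinuation occurs makes sense only if discontinued patients can be in the FAS.
- The two sets would differ in any case. Completion means that anaesthesia ended without departure from the protocol, and treatment changed for medical danger is classed as a deviation. Such a patient is not a completer but keeps the observation period.
- The main-analysis section offers a sensitivity analysis on all randomised patients, with the worst observed values filled in for missing AST.

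These points stand, with one limit: the sensitivity analysis is to be done only if needed and does not cover complications.

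It can also be said that safety reporting still captures harm. It covers mainly serious or unexpected events and those of grade 3 or higher, whereas the endpoint starts at grade II. The same section does not count events listed in the package insert. It is a separate duty and does not replace the endpoint.

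Finally, the number of patients may be small. Both drugs are standard care, known contraindications are excluded, and discontinuation can occur only during one anaesthetic. Nothing in the protocol links a suspected drug reaction to a higher AST peak. This limits the likely size and argues against treating the primary result as shown to be at risk. It does not remove the contradiction.

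**Conclusion.** Wrong as written; it should be fixed. Taken literally, the observation-period sentence leaves 28-day complications unobserved in the patients stopped for suspected drug harm. This contradicts the intention-to-treat principle, the rule against deregistration and the 28-day follow-up stated elsewhere.

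For AST, ALT and bilirubin the finding is ambiguity, not established loss. The 11 to 64 U/L applies only if the values are not used, and it rests on assumed numbers of patients and assumed AST excess. For complications, the statement that one or two patients could hold every event rests on the protocol's 1% rate. The number actually affected is unknown, because no discontinuation rate is given.

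**What to change.** Replace the second sentence of the observation-period paragraph with wording such as:

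> For all randomised patients, including those whose protocol treatment is discontinued or changed, the routine AST, ALT and bilirubin results of days 1–3 and complications to day 28 are collected. These patients are analysed in the FAS in their randomised group. Collection ends early only if consent to the use of data is withdrawn.

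This concerns collection of outcomes only and leaves the criterion for stopping treatment untouched. The cost is one sentence by amendment, with ethics committee approval. The blood tests are already routine and complications can be read from the chart, so no extra tests or visits are needed. The change is best made before any patient is discontinued, since complications that were not recorded may be hard to recover later.

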Upon receiving the report from the Principal Investigator, the Research Office will judge the urgency, importance, degree of impact, etc. of the report content, and if necessary, entrust the hospital director and the director to determine whether it is necessary to suspend registration or to notify the facility of information urgently.

- - 1. **Notifying Researchers in the Facility**

The Secretariat/Principal Investigator shall notify the Researcher in the Institute of the decision of the Secretariat/Principal Investigator in writing (e-mail is acceptable) regarding serious adverse events.

1. **Statistics**
   1. **Main analysis and criteria**

The main analysis is to compare the highest AST values within 3 days postoperatively in groups A and B by t-test, and judge a significant difference of less than 0.05 to be statistically significant. As a criterion for determining that the degree of IRI differs depending on the anesthetic, a difference of about AST 300 U / L was observed. This was based on the idea that a difference of about AST300U/L would have a significant impact on clinical anesthetic selection. If necessary, sensitivity analysis will include a population of patients who have completed protocol treatment (PPS), or a population of all randomized cases and supplemented with the worst values observed in groups A and B in cases where primary endpoint data are missing.

- 1. **Planned number of registrations, registration period, tracking period**

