As an important secondary endpoint, the highest ALT value within 3 days postoperatively for ischemia-reperfusion injury was compared in two groups by t-test, and a significant difference of less than 0.05 was statistically significant. For postoperative complications within 28 days, the Fisher test compares the two groups, with a significant difference of less than 0.05 as statistically significant. Regarding liver function, the highest bilirubin value within 3 days after surgery was compared in two groups by t-test, and a significant difference of less than 0.05 was considered statistically significant.

- 1. **Final Analysis**

In addition to the analyses described in 10.1 and 10.4, multivariate logistic analyses are performed to exclude the effects of non-anesthesia methods on IRI.

- 1. **End of research**

The research will end with the publication of all papers related to this study.

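### The rule that drops randomized patients without a postoperative AST also governs the complication comparison, so a patient with a known serious complication can be left out of it

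*Protocol*

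**What the plan says.** All references are to the protocol.

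- *Define the target population*: under the intention-to-treat label, "the analysis will be a population consisting of all randomized cases excluding cases with no data on the randomized primary endpoint". The sentence is not limited to the AST analysis. When discontinuations occur, a per-protocol set (PPS) of patients who completed protocol treatment is analyzed in addition.
- *Main analysis and criteria* (Statistics): if necessary, sensitivity analyses of AST use the PPS. The alternative named there is the "population of all randomized cases and supplemented with the worst values observed in groups A and B in cases where primary endpoint data are missing".
- *Analysis in secondary endpoints*: "For postoperative complications within 28 days, the Fisher test compares the two groups". ALT and bilirubin are compared by t-test. No population is named for any of the three, and no safety or all-treated set is defined elsewhere.
- *Primary outcome* (evaluation items): "the results of postoperative biochemical tests (tested daily for 3 days after surgery) that are usually performed in clinical practice will be used". No samples are drawn for the trial itself.
- *Criteria for Discontinuation of Protocol Treatment*: "Discontinue protocol treatment if adverse events are observed in which each group-assigned drug is suspected".
- *Observation period*: 28 days for complications, but "If protocol treatment is discontinued in any group, no observation period is set".

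**The concern.** Requiring an AST value is a reasonable condition for analyzing AST. It is not a reasonable condition for analyzing complications, because the two are observed separately: a complication can be known when no AST was drawn. Since AST comes only from routine sampling after surgery, it will be absent when the patient does not reach the first sample, and a severe event is one reason for that. The complication comparison is then restricted by a laboratory value whose absence can be a consequence of the complication. The set is called intention-to-treat, but for this endpoint it is a selected set, and the selection can only remove events from the count. What is at stake is the accuracy of the complication rates reported by arm.

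**Working it through.** **Step 1. Who is in which comparison, as written.**

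| Randomized patient | Main population | PPS | Complication test |
| --- | --- | --- | --- |
| Stopped early, any AST on days 1–3 | in | out | in, but no observation period is set, so day-28 data may be absent |
| Died or stopped during anesthesia, no AST | out | out | out |
| Completed anesthesia, then died or had a severe event before the first AST | out | in, if the PPS is not nested in the main population (not stated) | out |
| Never anesthetized, no AST | out | out | out, and no postoperative complication is possible |

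The second and third rows are the problem. The PPS does not solve it: it is formed only when discontinuations occur, the statistics section uses it only as a sensitivity analysis of AST, and it omits discontinued patients. The worst-value analysis does include all randomized patients, but it is optional and fills in AST only.

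**Step 2. How many events there are to lose.** Inputs: N = 56 (28 per group, from the sample-size section) and a grade 2 or higher rate p of about 1% (*Rationale for setting up endpoints*). The adverse-event section gives about 10% each for biliary fistula and infection, without grade, so 10% overall is shown as an assumed upper scenario.

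- Expected events, N × p: 56 × 0.01 = 0.56; 56 × 0.10 = 5.6.
- Chance of at least one event, 1 − (1 − p)^N: 1 − 0.99^56 = 0.430; 1 − 0.90^56 = 0.997.
- Chance of exactly one event at 1%: 56 × 0.01 × 0.99^55 = 0.32.
- Share of the expected count that one lost event represents at 10%: 1/5.6 = 18%.
- Effect on one arm with a single event: 1/28 = 3.6% becomes 0/27 = 0%.

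**Step 3. How often the rule would bite.** The expected number lost is N × P(complication and no AST). The protocol gives no value for this joint probability. The figures in Step 2 describe complications of any kind and are only a ceiling for it. For the death example alone, the adverse-event section prints a rate below 0/1%. Read as 0.1%, this gives fewer than 56 × 0.001 = 0.056 expected deaths.

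**Step 4. Effect on the Fisher test.** With 28 per arm, 5 versus 0 gives p = 0.051 and 6 versus 0 gives p = 0.023, so six events against none are needed. Removing one patient with an event leaves these values unchanged: 4/27 versus 0/28 gives p = 0.051, and 5/27 versus 0/28 gives p = 0.023. With few events expected, the test decision is unlikely to depend on the excluded patient.

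**The case against.** Several points against this are sound.

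- A reader might infer that the main population is the only one, and that anyone stopped early vanishes. The protocol does not support either. It names a PPS and an all-randomized AST analysis, and a patient with a single routine AST on days 1–3 stays in.
- A reader might take the 43% chance of any event as the size of the defect, or conclude that one exclusion would erase the whole count. The 43% ignores whether AST is missing. Erasing the count needs exactly one event (32% at the 1% rate) in a patient who also lacks AST. At a 10% rate that argument falls away.
- A reader might infer unequal losses by arm. This is possible for drug-related events, but nothing in the protocol shows it. Propofol induction is common to both arms, so airway failure at induction is not arm-specific.
- A reader might suppose that this trial's complication rate will be used to design the next trial. *Designing the next planned trial* makes that trial conditional on a difference in liver injury and does not say so.
- The endpoint is postoperative. If no operation takes place, it is unclear that any event can be scored. The adverse-event reporting section also does not count events listed in the package insert, so some drug reactions may be lost on that separate ground.
- Endpoint-specific populations are often left to an analysis plan.

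The last point does not dispose of the matter. The protocol is not silent here: it states an exclusion rule in general terms and offers no exception for complications. The other points limit the size of the problem and do not remove it.

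**Conclusion.** The point holds in a limited form. As written, a randomized patient with a known grade 2 or higher complication and no AST on days 1–3 is excluded from the complication comparison, and no other stated analysis of complications restores that patient. The same rule applies needlessly to ALT and bilirubin, though these follow the same sampling schedule as AST and would seldom differ in availability. The number affected is unknown and probably small. The consequence lies in the reported complication rates, where one event is a large share of 0.56 to 5.6 expected, and not in the Fisher decision. The primary AST comparison is not in question here.

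This rests on three assumptions: that the population rule covers the secondary endpoints because none other is named, that a death counts as a complication of grade 2 or higher, and that 10% is a fair upper scenario for the overall rate.

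**What to change.** 1. In *Define the target population*, limit the condition that primary-endpoint data exist to the AST analysis.
2. In *Analysis in secondary endpoints*, compare 28-day complications in all randomized patients in whom anesthesia was started, in the arm assigned, whether or not AST exists. Analyze ALT and bilirubin in all patients who have that measurement.
3. List randomized patients without AST by arm, with the reason and their complication status. This also shows anyone randomized but never anesthetized, whom item 2 leaves out.
4. In *Observation period*, change the sentence that sets no observation period after discontinuation, so that complications are recorded to day 28 for these patients too. Without this, items 1 and 2 cannot deliver the comparison for discontinued patients. It concerns data collection only, not when treatment is stopped.

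The cost is about one sentence in each section, slightly different denominators between endpoints, and a little more chart follow-up. Treatment, blood sampling and the primary analysis are unchanged.
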